# DEHyART trial: Study protocol for phase 2 randomised controlled study assessing the role of dose escalation using [18F] fluoromisonidazole positron emission tomography/computed tomography in head and neck cancers

**DOI:** 10.3332/ecancer.2025.1937

**Published:** 2025-07-02

**Keywords:** dose escalation, IMRT, HNSCC, radiotherapy, hypoxia, FMISO

## Abstract

**Background:**

Head and neck squamous cell carcinoma is often treated with radiotherapy, frequently combined with chemotherapy, to improve overall survival (OS). Despite advancements, locoregional control (LRC) remains a significant challenge, with 15%–50% of patients experiencing locoregional recurrence, negatively impacting OS and quality of life. Hypoxia within tumor cells is a critical factor contributing to treatment failure, necessitating higher radiation doses to achieve similar therapeutic effects as in normoxic cells. This study aims to investigate the role of dose escalation using [18F] fluoromisonidazole (FMISO) positron emission tomography/computed tomography (PET CT) to target hypoxic sub-volumes in head and neck cancer (HNC) to improve LRC.

**Methods:**

The dose-escalated hypoxia-adjusted radiotherapy trial is an open-label, parallel, randomised, single-centre, phase II study. Patients with HNC will undergo [18F]. FMISO PET CT to identify hypoxic regions. Normoxic patients will be labeled as Arm 1 and will not be part of the primary assessment. Patients with hypoxia will be stratified into two arms (2 and 3). Arm 2 will receive standard radiotherapy of 70 Gy in 2 Gy fractions, while Arm 3 will receive an additional boost to the hypoxic sub-volumes, delivering a total of 80 Gy (Phase 2). All patients in Arms 2 and 3 will also receive concurrent chemotherapy with cisplatin. Patients will be monitored weekly for treatment tolerance, with acute adverse events recorded according to National Cancer Institute Common Terminology Criteria for Adverse Events v5.0. The primary endpoint is LRC, defined as the time from randomisation to the first histopathologically confirmed relapse of locoregional disease. Secondary endpoints include OS, locoregional relapse-free survival, acute and late toxicity and patient-reported outcomes assessed using the European Organisation for Research and Treatment of Cancer QLQ-C30 and QLQ-H&N35 questionnaires.

**Discussion:**

This study addresses a critical gap in the management of HNC by targeting hypoxic regions within tumours, potentially improving LRC and, consequently, OS. The use of [18F] FMISO PET CT for identifying hypoxic sub-volumes allows for tailored radiation dose escalation, which could overcome the radioresistance associated with hypoxia. By comparing outcomes among standard radiotherapy (Arm 2) and dose-escalated treatment (Arm 3), this trial aims to establish a more effective therapeutic strategy for HNC patients.

**Trial registration:**

This trial is registered with the Clinical Trials Registry of India (CTRI/2024/04/065373), registered on 08^th^ April 2024 on ctri.nic.in and clinicaltrials.gov (NCT06087614) registered on 18th September 2023 on clinicaltrials.gov.

## Introduction

### Background and rationale

Radiotherapy is the mainstay in treating head and neck squamous cell carcinoma (HNSCC). The concurrent chemotherapy with radiotherapy gives an additional absolute survival benefit of 6.5% at 5 years [1]. Despite advancements in radiation and chemotherapy, the overall survival (OS) in HNSCC has been dismal. Locoregional control (LRC) drives the overall survival in most head and neck squamous cell carcinoma, however, it is reported that about 15%–50% of patients fail locoregionally [2,3,4].

Locoregional recurrence not only causes a drop in OS but is also a major concern for adding overall morbidity and deteriorating patients’ quality of life. Therefore, further improving on LRC would be a prudent therapeutic strategy for increasing OS and enhancing the quality-of-life indices. The authors assessed the pattern of failure for HNSCC being treated with intensity-modulated radiotherapy (IMRT). They found that with a 3-year LRC of 48.9%, most failed in the high-dose region (69.2%), suggesting inherent biological resistance to treatment [5,6]. One hypothesised reason for this treatment failure is the presence of hypoxia in tumour cell lines, which may necessitate three times the radiation dose to achieve an isotherapeutic effect comparable to that in normoxic cells [7].

### Hypoxia in head and neck patients

Tumour hypoxia is a major risk factor for local and distant failure after radiotherapy [8]. It is reported that up to 80% of HNSCC have baseline hypoxia, with sites like hypopharyngeal and oropharyngeal having a higher incidence of hypoxia than the other sites of the head and neck [9]. Non-invasive hypoxia assessment in head and neck cancer (HNC) has been extensively conducted using various radioactive tracers such as [18F] fluoromisonidazole (FMISO), [18F] fluoroazomycin-arabinoside (FAZA) and [18F] HX4. These have been individually studied in various studies [10–14] and have been correlated with other hypoxia biomarkers in numerous studies as well [15–17]. A recent meta-analysis showed that positron emission tomography (PET)-measured hypoxia with FMISO or FAZA strongly impacted OS and LRC in HNSCC. Most trials have used FAZA and FMISO, which have shown equivalence in multicentre trials [18]. The meta-analysis by Zschaeck *et al* [18]. showed that the hypoxia PET parameter was an independent risk factor in multivariate analysis, irrespective of any established clinical parameter. Studies have investigated whether subsequent recurrences overlap with the initial hypoxic volumes, yielding discordant results. Boeke *et al* [19]. reported a high median overlap of 42%, while two other studies [20, 21] found no significant overlap. Nishikawa *et al* [22] demonstrated that an initial tissue-to-muscle ratio (TMR) greater than 2.42 could predict failure in terms of spatial location. These findings underscore the need for a second FMISO scan during the course of radiotherapy, which may better predict chronic hypoxia. Considering the significant influence of tumour-associated hypoxia on the response of HNSCCs to radiotherapy, different treatment strategies have been proposed and tested in exploratory analyses, trying to identify the stability of these sub-volumes over multiple fractions and the possibility of escalating treatment doses to high-risk hypoxic sub-volumes (HSVs) [23–25].

### Rationale for dose escalation in HNC

Theoretical planning studies have been conducted to assess the dose escalation to the biology-selected FMISO volumes [26–28]. Thorwarth *et al* [27] predicted the increase in tumour control probability from 55.9% to 70.9% by increasing the dose up to 84 Gy to the FMISO-selected hypoxic volumes. In a recent Phase II randomised study by Welz *et al* [29], escalated doses to the hypoxic volumes determined by FMISO. The authors escalated doses to this volume to 77 Gy (2.2 Gy per fraction) by the simultaneous integrated boost technique and compared it to standard fractionation and doses. There was a non-significant increase in 5-year local control favouring dose dose-escalated arm. However, the study was prematurely closed due to poor accrual. Another flaw in the study design could be a marginal increase in dose escalation, with a 2% mean dose escalation against a planned 10% dose escalation. The mean hypoxic volume subjected to dose escalation was 2.9 ml, which might be too small to make any significant difference in outcomes. An ongoing phase III trial, ESCALOX [30], assesses dose escalation to the hypoxic volumes to a dose of 80.5 Gy and is currently accruing patients.

### Objectives

There exists a critical need to increase LRC in HNC while maintaining the patients’ quality of life. Numerous studies [31–33] have investigated dose and volume modifications in p16-positive oropharyngeal cancers. However, there is a paucity of literature addressing these modifications in p16-negative oropharyngeal and non-oropharyngeal tumours, underscoring a significant research gap. The primary objective of this study – DEHyART is to assess the role of dose escalation using [18F]. FMISO positron emission tomography/computed tomography (PET CT) in HNC to improve LRC by targeting HSV. Specifically, the study aims to evaluate whether increasing the radiation dose to hypoxic areas within tumours, identified through FMISO PET CT, can enhance treatment outcomes in terms of LRC compared to standard treatment.

The secondary objectives include evaluating the impact of this treatment on overall survival, acute and late toxicity, and patient-reported outcomes such as quality of life. The study also aims to compare the outcomes between the dose-escalated group and the standard treatment group in a randomised controlled trial setting.

## Study/Trial design

DE-HyART is an open-label, parallel, randomised, single-centre, phase II study designed to evaluate the effectiveness and feasibility of dose escalation using FMISO PET scans for HNC. This superiority trial aims to assess the impact of integrating IMRT with simultaneous integrated boost (SIB) and dose escalation to hypoxic sub-volumes, as delineated by [18-F] FMISO, compared to standard-dose radiotherapy. The treatment protocol also incorporates concurrent chemotherapy with standard dosing of the physician’s choice and patients’ fitness. The protocol has been developed in accordance with SPIRIT guidelines [34, 35].

### Participants, interventions and outcomes

DE-HyART is an investigator-initiated study coordinated by the Department of Radiation Oncology at Rajiv Gandhi Cancer Institute and Research Centre, Delhi. The department will oversee the entire study, including registration, data management and radio-oncological quality assurance. The study has received approval from the Scientific Review Board and Institutional Review Board (IRB) for scientific and ethical compliance. All participants will provide written informed consent prior to enrollment, which will outline the randomised nature, scope and potential consequences of the study taken by the principal investigator or research coordinator. The flow of the study will be as mentioned in Table 1 and Figure 1.

### Eligibility criteria

All HNC patients planned for radical radiotherapy (± concurrent chemotherapy) in the department of radiation oncology were screened as per the inclusion and exclusion criteria mentioned in Table 2.

### Participant screening, recruitment and consent [18F] FMISO PET CT and hypoxia identification

All eligible patients will be subjected to screening [18F] FMISO scan, labelled as baseline FMISO. The primary challenge with using FMISO is its lipophilic nature, which slows its clearance from normal tissues such as blood and muscle, resulting in a low signal-to-background ratio. Numerous studies [12, 36–39] have evaluated FMISO parameters with clinical endpoints, demonstrating that a TMR ranging from 1.2 to 1.6 significantly correlates with the reduction of hypoxic volumes during the course of radiotherapy.

Therefore, a TMR of 1.4 will be employed to differentiate hypoxic from normoxic patients (TMR ≥ 1.4 and < 1.4 will be labelled as hypoxic and normoxic, respectively). Standardised assessment of SUVmax and SUVmean will be utilised. Tumour SUVmax will be determined by generating a region of interest (ROI) of 1 cm^2^ at the most metabolically active region of the tumour. For background reference, the contralateral sternocleidomastoid muscle at the caudal edge of the hyoid bone will be used, with a similar ROI to calculate the TMR.

### Timing of [18F] FMISO PET CT

All enrolled patients will undergo an [18F] FMISO PET CT scan. Patients exhibiting hypoxia, as determined by the PET results, will be randomised into either Arm 2 or Arm 3. A second [18F] FMISO PET CT scan will be performed between the fourth and fifth weeks of radiation therapy to evaluate the temporal variability of HSV.

## Arm allocation and randomisation

Depending upon the result of the baseline FMISO, the patient will be either hypoxic or normoxic. Patients exhibiting no hypoxia (TMR < 1.4) in their tumour will be labelled as Arm 1 and act as an external cohort. Patients with hypoxia (TMR ≥ 1.4) will be stratified by T stage, N stage and tumour site, then randomly assigned in a 1:1 ratio to either Arm 2 or Arm 3 using a computer-generated randomisation sequence to ensure balanced distribution across these variables. Both arms will be subjected to chemoradiation by IMRT and concurrent chemotherapy with cisplatin at 40 mg/m^2^. In Arm 3, the trial arm will receive an additional dose of 10 Gy @ 2 Gy per fraction in phase II (total 80 Gy) to the HSV + 5mm isotropic margin.

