## Sample size

Estimated LC rates 59% and 84% in the control and treatment arm, respectively, in the phase II study by Welz *et al* [29]. For achieving an 80% power (i.e., 1−β = 0.8) at the 5% level of significance (i.e., α = 0.05) with the equal allocation (i.e., k = 1), the sample size for Arm 2 and 3 is 62 patients in each arm. This study is designed as a Phase II trial aimed at evaluating the preliminary efficacy and safety of the intervention. As such, the primary focus is on detecting a signal of LRC rather than establishing a long-term survival benefit. The sample size of 124 participants (62 per group) is consistent with Phase II study designs, which typically involve smaller cohorts to efficiently assess early efficacy. Due to the exploratory nature of this trial, the follow-up period was set at 2 years to capture early control rates, which are increasingly recognised as predictive of long-term outcomes in salivary ductal cancers. The 2-year endpoint aligns with the study’s goal of generating data to inform the feasibility of subsequent Phase III trials.

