### Data collection and analysis

All data will be collected in the central registry of the institute and anonymised. All statistical analyses were performed using the Statistical Package for Social Science System (SPSS v26, SPSS Inc, Chicago, IL) or equivalent software. Continuous variables will be written as mean (along with standard deviation) and median (along with interquartile range). Categorical variables will be represented as frequencies and percentages. Inter-cohort testing will be performed using chi-square for categorical variables and independent-t/nonparametric tests for continuous variables. Time-to-event endpoints will be measured from the date of randomisation to the date of failure or last follow-up. The LRC rate at 2 years will be estimated using the Kaplan–Meier method, with the time to locoregional failure defined as the duration from the start of radiation therapy to the first documented recurrence or progression within the primary tumour site or regional lymph nodes. The LRFS and OS, as mentioned earlier, death from any cause will be considered a failure. The LRFS and the OS rates will be estimated using the Kaplan–Meier product-limit method for each arm. Their distributions will be compared between treatment arms (Arms 2 and 3) with a two-sided log-rank test ≤ 0.05. The clinicopathological characteristics, survival outcomes and treatment modalities will be analysed using the univariate and multivariate Cox proportional hazards model. All eligible patients will be included in the analysis in the arm to which they were randomly assigned (intent-to-treat).

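### Randomisation is stratified by T stage, N stage and tumour site, but the stated arm comparison does not use these factors: a conservative test and a modest loss of power

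*Protocol article*

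**What the plan says.** Under Arm allocation and randomisation, patients with hypoxia "will be stratified by T stage, N stage and tumour site, then randomly assigned in a 1:1 ratio" to Arm 2 or Arm 3. The stated means is a "computer-generated randomisation sequence to ensure balanced distribution across these variables". The article does not give the number of levels per factor or the blocking method.

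Under Data collection and analysis:

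- **LRFS and OS (secondary):** "The LRFS and the OS rates will be estimated using the Kaplan–Meier product-limit method for each arm", followed by "Their distributions will be compared between treatment arms (Arms 2 and 3) with a two-sided log-rank test ≤ 0.05". The randomisation factors are not mentioned.
- **LRC (primary):** "The LRC rate at 2 years will be estimated using the Kaplan–Meier method". No test between arms is named.
- **Modelling:** disease characteristics, survival outcomes and treatment "will be analysed using the univariate and multivariate Cox proportional hazards model". The covariates are not listed, and the model is not called the treatment comparison.

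Under Sample size: "Estimated LC rates 59% and 84% in the control and treatment arm", 80% power, 5% significance and 62 patients per arm.

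**The concern.** T stage, N stage and site were presumably chosen because they are expected to predict outcome. Stratified allocation removes most of the chance imbalance in them, so the observed treatment difference varies less between repetitions of the trial. A log-rank test that ignores the factors still uses a variance that includes their contribution. Its standard error is then too large, its true type I error falls below 5%, and it gives up some of the precision that the stratification bought.

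There is a second, smaller issue. A log-rank test stands beside a multivariable Cox model with open covariates and no stated hierarchy, in an open-label trial. As the article reads, the adjusted estimate of the arm effect could be specified after the data are seen.

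**Working it through.** **1. The design figures.** Inputs from Sample size: p1 = 0.59, p2 = 0.84, alpha 0.05 (taken as two-sided), power 0.80, 1:1 allocation. The mean proportion is 0.715.

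The pooled two-proportion formula is n = [1.96 √(2 × 0.715 × 0.285) + 0.8416 √(0.59 × 0.41 + 0.84 × 0.16)]² / 0.25² = (1.251 + 0.516)² / 0.0625 ≈ 50 per arm, or 58 with continuity correction. The stated 62 is not reproduced. That is a separate matter, and 62 is used below as given.

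- Power of the two-proportion test at 62 per arm: Φ[(0.25 √62 − 1.251) / 0.613] = Φ(1.17) = 87.9%.
- Hazard ratio implied under proportional hazards: ln 0.84 / ln 0.59 = 0.330.
- Expected events: 62 × (0.41 + 0.16) = 35.3.
- Schoenfeld power: Φ(√35.3 / 2 × |ln 0.330| − 1.96) = Φ(1.33), about 91%.

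**2. Why the plain test is conservative.** If the unstratified log-rank z has null variance V instead of 1, its true two-sided size is 2[1 − Φ(1.96 / √V)]. Simulation used 124 patients, 12 cells (2 × 2 × 3), blocks of 4 within cells and 8,000 replicates. The three sites come from Table 2. The two levels each for T and N, the blocks and the prognostic strengths are assumptions.

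| HR for T and for N | V | Size from formula | Size simulated |
|---|---|---|---|
| 1.5 | 0.964 | 4.6% | 4.6% |
| 2.0 | 0.880 | 3.7% | 3.7% |
| 3.0 | 0.772 | 2.6% | 2.5% |

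**3. Stratified log-rank on 12 strata.** Marginal control rates were held at 59% and 84%, with 2 years of follow-up and 4,000 replicates. Each cell shows unstratified v stratified. The factor HR compares the highest with the lowest level of each factor.

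| Factor HR | Type I error | Power |
|---|---|---|
| 1.0 | 5.1 v 5.4% | 88.8 v 88.2% |
| 1.5 | 4.6 v 5.0% | 89.1 v 89.1% |
| 2.0 | 3.2 v 4.8% | 89.3 v 90.4% |
| 3.0 | 2.6 v 4.8% | 91.1 v 94.5% |

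**4. Cox score test with collapsed main effects.** Power is shown as unadjusted log-rank v adjusted score test, with 3,000 replicates. Censoring of 0.006 per month and the stage mix are assumed.

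| HR for T, N, site | 59% v 84%, 12 cells | 59% v 84%, 48 cells | 59% v 80%, 48 cells |
|---|---|---|---|
| 1.5, 1.5, 1.3 | 86.9 v 88.1% | 88.3 v 88.7% | 71.0 v 73.3% |
| 2, 2, 1.5 | 86.5 v 89.1% | 86.2 v 88.9% | 71.5 v 75.5% |
| 3, 3, 2 | 89.7 v 93.8% | 87.5 v 92.7% | 71.6 v 80.8% |

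At the protocol's rates with 12 cells the gain is 1.2, 2.6 and 4.1 points. With allocation in 48 cells it is 0.4, 2.7 and 5.2 points. The 59% v 80% column is an assumed smaller effect, where the gain is 2.3, 4.0 and 9.2 points. Null rejection across both layouts was 2.7 to 5.2% unadjusted and 4.9 to 5.9% adjusted. A further run with 12 cells gave 5.4 to 5.9% adjusted.

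**5. Stratifying the test on every cell.** With four T levels, four N levels and three sites there are 48 cells, so 124 / 48 = 2.6 patients and 35 / 48 = 0.7 events per cell. Power, unstratified v fully stratified, was 88.0 v 78.5%, 87.8 v 78.2%, 89.6 v 81.2% and 90.1 v 83.6% for factor HRs of 1.0, 1.5, 2.0 and 3.0. That is a loss of 6.5 to 9.6 points.

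Monte Carlo error is about 0.3 to 0.8 points throughout.

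**The case against.** The strongest reply is that the article never calls the log-rank test unstratified. Strata, covariates and stage groupings are commonly left to the analysis plan or full protocol, which are not shown. The Cox sentence also includes treatment among what will be modelled, so an adjusted estimate may already be intended. The error is on the safe side, and power exceeds the 80% target without adjustment.

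Much of this stands. False positives are not inflated, the gain is modest, and an unseen plan may already adjust. What does not stand is that the article is merely silent. It fixes the test, its sidedness, its level and the analysis set, so a reader would take the comparison as a plain log-rank test, and a better method is available at almost no cost.

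A reader might also infer more than the documents support:

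- **That the primary comparison is an unstratified log-rank test.** The log-rank sentence refers to LRFS and OS. For LRC no test is named.
- **That the trial falls short of 80% power for this reason.** A simulation with a hazard ratio of 0.40 gives the plain test 76%, but the protocol's rates imply 0.33, and there the plain test has about 86 to 91%.
- **That the strata are too many and the allocation should change.** The article gives neither levels nor blocks, so the 48-cell layout is only a possibility.
- **That any stratified test would gain power.** Step 5 of the working shows the reverse for full cross-stratification.

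**Conclusion.** The point holds as a modest, inexpensive improvement. The factors used to stratify randomisation are not carried into the stated comparison of LRFS and OS, and no arm comparison of LRC is named that could carry them. If they are prognostic, the plain log-rank test has a true type I error of about 3 to 5% and gives up about 0 to 4 points of power at 59% v 84%, with power above 80% either way. The largest loss at those rates, about 5 points, came with the strongest factors and allocation in 48 cells. At an assumed 59% v 80% with strong factors it reached about 9 points.

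These sizes rest on assumed prognostic strengths, stage groupings, block size and, in part, dropout. They were simulated at the control rates used for the sample size; for LRFS and OS the direction carries over but the size may differ. If the factors had no prognostic value there would be essentially nothing to gain.

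**What to change.** For LRC, LRFS and OS, pre-specify the Arm 2 v Arm 3 comparison in one of two ways:

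- a Cox model with treatment plus T stage, N stage and site as main effects in a few collapsed levels, tested by the score or likelihood-ratio test; or
- a log-rank test stratified on a few collapsed strata.

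State the collapsed levels in advance and keep the unadjusted log-rank test as a sensitivity analysis. For LRC this also supplies the missing named test. Do not stratify the test on every T by N by site cell, and leave the allocation unchanged.

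The cost is a short addition to the analysis text and slightly more analysis work. T stage, N stage and site are known at baseline because they are used at randomisation, so no new data are needed. The one statistical downside is that null rejection may sit marginally above nominal, about 5.4 to 5.9% in simulation. The score or likelihood-ratio test is preferred to the Wald test, which rejected in 5 to 7% of null trials.

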## Intervention

All patients will be treated using IMRT (with pre-specified image guidance protocol as per institutional standards).

## Arm 1

Patients will receive standard care and serve as external controls, representing typical clinical practice. Their cases will be reviewed in the head and neck multidisciplinary clinic, following the institutional approach. These patients will undergo treatment analogous to that of ‘Arm 2,’ but with allowances for protocol deviations at the discretion of the treating radiation oncologist.

## Arm 2

The prescribed radiotherapy dose will be 70 Gy, delivered in daily fractions of 2 Gy. The elective volume will receive 50 Gy, administered in 2 Gy daily fractions over the first 5 weeks. This will be followed by a boost to the high-risk volume, delivering an additional 20 Gy in 2 Gy daily fractions over the subsequent 2 weeks. The entire treatment will be delivered in a phased approach using sequential planning.

## Arm 3

The radiation dose will be similar to ‘Arm 2’. In addition, the HSV identified on baseline FMISO scans will be contoured and an isotropic margin of 3 mm will be given. This volume will be boosted in phase II to a total dose of 80 Gy. (Addition of 30 Gy in 3 Gy daily fraction added in phase II as a simultaneous integrated boost – SIB) (Figure 2). The BED and EQD2 for Arm 3 (to HSV) are 99 Gy_10_ and 82.5Gy, respectively, in comparison to 84 Gy_10_ and 70 Gy, respectively, in Arm 2.

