## Contouring protocol

The patients will be immobilised using a four-clip thermoplastic cast (Orfit Ray™ Cast) as per standard institutional protocol. The treatment planning scans will be performed with IV contrast and 3 mm slice thickness. Daily IGRT is not mandatory but recommended. The daily shift should be at most 5mm of the planning target volume in any axes.

Arm 2 and 3: Gross tumour volume (GTV) will be delineated using MRI and FDG PET CT per standard institutional standards. Clinical target volume (CTV 1) will include GTV based on clinical and radiologic information (including primary tumour and involved lymph nodes), expanded with isotropic 5-mm margins. Clinical target volume (CTV 2) will consist of the high-risk areas harbouring microscopic disease and elective nodal regions. CTV 2 will be created individually for the primary target and the secondary lymphatic. A 5 mm margin will be added to each CTV 1 and 2 to form planning target volume (PTV) 1 and 2, respectively. A model dose of 50 Gy in 25 fractions will be prescribed to PTV 2 in phase I and 20 Gy in 10 fractions to PTV 1 in phase II.

Hypoxic sub-volume delineation (Arm 3): The HSV delineation will be done for patients in arm 3 using baseline FMISO. The HSV will be contoured as per baseline FMISO and adjusted according to the second FMISO scan done between the fourth and the fifth week of radiation treatment. A planning CT will also be repeated at the time for adjusting the HSV to account for temporal changes. The HSV, thus, delineated will be isotropically enlarged by 3 mm to form a biological target volume (BTV). The BTV will be truncated from bone, air and organs at risk (OAR) by 3mm. The BTV will be prescribed 30 Gy in 10 fractions.

Adjusting HSV in phase 2*:* The HSV will not be adapted based on the response, but will be adjusted only to account for geometrical changes due to image registration in the new scan taking into account – OARs, air and bone. The boost volume will primarily remain consistent with the baseline HSV.

Organ at risk: Dose constraints to OAR and planning risk volume will be taken from quantitative analysis of normal tissue effects in the clinic (QUANTEC) and RTOG protocols (wherever QUANTEC did not provide constraints). The patients in ‘Arm 3’ will be subjected to isotoxic dose escalation, with constraints remaining the same as Arm 2.

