**Figure 2. figure2:**
[figure not shown]
(a–c) shows 18F FDG PET CT images in axial, coronal and sagittal views, respectively. (d–f) shows 18F FMISO PET CT images in axial, coronal and sagittal views, respectively. (g–i), target delineation as labeled in axial, coronal and sagittal views, respectively. GTV – Gross Tumour Volume, HSV – Hypoxic Sub-Volume, Ph I 50 Gy – Volume receiving 50 Gy in 25 fractions in phase 1, Ph II 20Gy – Volume receiving 20 Gy in 10 fractions in phase 2. Ph II 30Gy – Volume receiving 30 Gy in 10 fractions in phase 2.

**Table 1. table1:** Schedule of enrolment, interventions, and assessments for the DEHyART study as per SPIRIT guidelines.

Time points	Study period														
	Enrolment	Allocation	Post allocation (During RT)								Acute phase (Post RT)		Late phase (Post RT)		
	Pre RT	Pre RT	Week								Month		Month		
			1	2	3	4	5	6	7	Post RT 2	3	6	12	18	24
Enrolment															
Eligibility screen	X														
Informed consent	X														
Diagnostic/staging workup	X														
CCI	X														
F MISO PET CT (baseline)	X														
Allocation															
Randomisation		X													
Intervention															
Arm 1 (CRT)			X	X	X	X	X	X	X						
Arm 2 (CRT)			X	X	X	X	X	X	X						
Arm 3 (CRT)			X	X	X	X	X	X	X						
Dose escalation (Arm 3)							X	X	X						
Second F MISO PET CT (Arm 3)						X									
Assessment															
CTCAE v5 (acute toxicity)		X				X			X	X	X	X			
EORTC QLQ C30 and HN35		X				X			X	X	X	X	X	X	X
MDADI		X				X			X	X	X	X	X	X	X
RTOG (late toxicity)													X	X	X
Response assessment (Clinical ± radiological)											X	X	X	X	X

**Table 2: table2:** Inclusion and exclusion criteria for enrolment in DEHyART study.

Inclusion criteria	Exclusion criteria

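### The Arm 3 boost, the only planned difference between the randomised arms, is prescribed in two incompatible ways (fractionation and margin)

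*Protocol article*

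**What the plan says.** **Boost fractionation and margin**
- Arm allocation and randomisation: Arm 3 receives an "additional dose of 10 Gy @ 2 Gy per fraction in phase II (total 80 Gy) to the HSV + 5mm isotropic margin".
- Intervention, Arm 3: "Addition of 30 Gy in 3 Gy daily fraction added in phase II as a simultaneous integrated boost", with the boosted volume brought to 80 Gy in total. On the margin: "an isotropic margin of 3 mm will be given". The same paragraph states 99 Gy10 (BED) and 82.5 Gy (EQD2) to the HSV, against 84 Gy10 and 70 Gy in Arm 2.
- Contouring protocol: the HSV is enlarged by 3 mm, trimmed from bone, air and organs at risk, and prescribed 30 Gy in 10 fractions. The Figure 2 legend repeats 30 Gy in 10 fractions.

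**Lesser points**
- Weeks: Intervention puts phase I in the first five weeks and phase II in the next two. Table 1 marks Arm 3 dose escalation in weeks 5, 6 and 7.
- Chemotherapy: the abstract's Methods say "All patients in Arms 2 and 3 will also receive concurrent chemotherapy with cisplatin", and Arm allocation and randomisation fixes cisplatin at 40 mg/m². Study/Trial design says "concurrent chemotherapy with standard dosing of the physician’s choice" and adds patient fitness.
- HSV rule: the Contouring protocol says the HSV is "adjusted according to the second FMISO scan done between the fourth and the fifth week of radiation treatment". Two paragraphs later it says "The HSV will not be adapted based on the response, but will be adjusted only to account for geometrical changes".

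**The concern.** Arms 2 and 3 share the base radiotherapy and the chemotherapy. The boost is the only planned difference, so the locoregional control (LRC) comparison estimates the effect of whatever boost is given. If the protocol defines that boost in two ways, the result may not belong to a single regimen.

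The protocol itself treats these details as decisive. In its rationale for dose escalation it faults an earlier randomised trial because the mean escalation reached 2% against a planned 10%, and because the mean boosted volume of 2.9 ml may have been too small. Dose per fraction and margin set the biological dose and the boosted volume, and these are the items on which the sections disagree. The shared total of 80 Gy makes the disagreement easy to miss. It also weakens plan checking: the trial committee is to check radiation plans, but the published text gives it two specifications to check against.

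**Working it through.** **Step 1. Biological dose.** The Gy10 notation implies an alpha/beta ratio of 10. With n fractions of d Gy and no correction for overall time:

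BED = sum of n × d × (1 + d/10); EQD2 = BED / 1.2.

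The first two rows reproduce the protocol's own figures.

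| Dose to the HSV | Source | Arithmetic | BED (Gy10) | EQD2 (Gy) | Stated figure |
|---|---|---|---|---|---|
| 35 × 2 Gy | Arm 2 | 70 × 1.2 | 84 | 70 | matches |
| 25 × 2 + 10 × 3 Gy | Intervention; Contouring protocol | 50 × 1.2 + 30 × 1.3 = 60 + 39 | 99 | 82.5 | matches |
| 40 × 2 Gy | Arm allocation, as five further fractions | 80 × 1.2 | 96 | 80 | does not match |
| 30 × 2 + 5 × 4 Gy | Arm allocation, as 2 Gy added on five phase II days | 60 × 1.2 + 20 × 1.4 = 72 + 28 | 100 | 83.3 | does not match |

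The EQD2 gain over Arm 2 is 82.5 − 70 = 12.5 Gy for the Intervention schedule and 80 − 70 = 10 Gy for the 40-fraction reading. Neither reading of the allocation sentence gives 99 Gy10.

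**Step 2. Treatment time.** Phase I is 50 / 2 = 25 fractions in 5 weeks, or 5 per week. Thirty-five fractions take 7 weeks, as Intervention and Table 1 show. The 40-fraction reading would take 8 weeks, which neither shows. The allocation sentence does not say whether its fractions are extra treatment days, so the added week belongs to one reading only.

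**Step 3. Margin.** The protocol gives no HSV size for this trial, so I assume a sphere and show a range. With r = (3V / 4π)^(1/3), the expanded volume is (4/3)π(r + margin)³.

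| HSV (ml) | r (cm) | +3 mm (ml) | +5 mm (ml) | Ratio |
|---|---|---|---|---|
| 1 | 0.620 | 3.27 | 5.89 | 1.80 |
| 2.9 | 0.885 | 6.96 | 11.12 | 1.60 |
| 10 | 1.337 | 18.36 | 25.95 | 1.41 |
| 20 | 1.684 | 32.71 | 43.63 | 1.33 |

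The 2.9 ml row uses the mean volume quoted from the earlier trial. All volumes are before trimming from bone, air and organs at risk.

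**Step 4. Weeks.** Ten phase II fractions at 5 per week fill two weeks, 6 and 7. Table 1 has three marks. Placing the first in week 5 relies on column positions in a table read from PDF; the count of three does not.

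**Step 5. Chemotherapy.** Two places name cisplatin for both randomised arms, one with a dose. A third leaves dosing to the physician and the patient's fitness. The statements differ on who decides, but all apply to both arms.

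**Step 6. HSV rule.** The later paragraph limits adjustment to geometry and keeps the boost largely at the baseline HSV. It can be read as explaining the earlier sentence. The earlier references to the second scan and to changes over time still fit it loosely.

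**The case against.** The best defence is that only one sentence is out of line. The Arm 3 intervention text, the contouring prescription, the Figure 2 legend and the stated BED and EQD2 agree on fractionation, and the first two agree on margin. The allocation sentence shares the target, the phase and the 80 Gy total, and could be shorthand for the 10 Gy increment over Arm 2. The article is also not the operating document. Protocol version 1.2 is in use, a committee checks plans, and Arm 3 keeps the organ-at-risk constraints of Arm 2.

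Much of this stands, and it limits what can be said about harm. The shorthand reading fails, however. Under the integrated boost the increment is (30 − 20) / 10 = 1 Gy per fraction over ten fractions, whereas the sentence says 2 Gy per fraction, which is five. It does nothing to explain 5 mm against 3 mm.

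A reader might infer more than the text supports:
- **That 30 Gy comes on top of the 20 Gy of phase II.** The wording is loose, but delivered simultaneously this would be 25 × 2 + 10 × 5 Gy, or 60 + 75 = 135 Gy10. The same paragraph rules it out with its 80 Gy total and 99 Gy10.
- **That chemotherapy biases the comparison.** No passage says it is chosen after allocation, and no imbalance is shown. In an open-label trial this is a risk only.
- **That the HSV rule is a flat contradiction.** The later paragraph may be a clarification.

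**Conclusion.** The concern holds for fractionation and margin. The section Arm allocation and randomisation contradicts the Intervention and Contouring sections on both, and the Figure 2 legend on fractionation. The difference is 96 against 99 Gy10 (80 against 82.5 Gy EQD2) if the allocation sentence means 40 fractions of 2 Gy. For a spherical HSV of 1 to 20 ml, the two margins give a boost volume ratio of 1.8 to 1.3 before trimming. The contradiction itself rests on the text alone. Only its size depends on the alpha/beta of 10, the reading of the allocation sentence and the spherical shape.

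The weeks in Table 1 and the chemotherapy statements are real but secondary inconsistencies. The HSV-adjustment wording needs aligning, no more.

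It may be tempting to conclude that Arm 3 patients have received different treatments. The documents show neither that nor the opposite. Because the contradiction lies in the definition of the tested treatment, and patients are already being treated, it must be corrected. This review takes no view on which fractionation, margin or chemotherapy statement is right.

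**What to change.** 1. The sponsor should check whether protocol version 1.2 carries the same conflict. It should then reconcile Arm allocation and randomisation, Intervention (Arm 3), Contouring protocol and Table 1 to one boost fractionation, one margin and one week range, and recalculate the BED and EQD2 if the reconciled schedule requires it.
2. Reconcile the abstract's Methods, Study/Trial design and Arm allocation and randomisation to one chemotherapy statement. If any choice remains, record it before allocation.
3. Align the Contouring protocol's sentence on the second FMISO scan with its geometry-only paragraph.
4. Tabulate the fractionation and margin actually used for each Arm 3 patient treated since March 2024, and report the table with the primary result. The planned intention-to-treat comparison need not change.

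The cost is a text correction and a chart check of treated Arm 3 patients. No new patient procedures are needed.
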